### Sample size and power

The *R* package *simr* [56] was used for power calculations, which simulated a multilevel model with time and group as fixed effects. The primary outcomes are anxiety and depressive symptoms, indexed by GAD-7 and PHQ-9 scores, respectively. Given the low-intensity nature of the Digital PAI and its evaluation against a Self-Monitoring Placebo as a placebo control [57], we expected the between-treatment effect sizes to range from small (Cohen’s *d* = 0.2) [26, 58] to moderate (*d* = 0.5) [24]. To achieve a statistical power of 81% while detecting small to moderate between-group efficacy effect sizes at a 5% significance level, a sample size of between 300 and 1,600 is required. Accounting for an estimated 50% attrition rate, our planned sample size was 1,200 (600 participants per group).

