### Statistical analysis plan

#### Data processing and missing data management

All preprocessing steps and data analyses will be conducted using the *R* software [113]. Using an intention-to-treat (ITT) approach, we will estimate between-group treatment efficacy for continuous and binary clinical outcomes [114]. A complier average causal effects (CACE) analysis will also be conducted to determine treatment efficacy between high- and low-potential engagers [115]. Before conducting the key data analyses, a series of preprocessing steps will be undertaken. These include anomaly diagnostics, assumption checks (e.g., linearity, multivariate normality), and random forest imputation of missing data. Random forest imputation with the *missRanger* package [116] will be used instead of multiple imputation because it better handles nonlinear associations and interactions and generates improved performance even under missing not-at-random (MNAR) conditions [117]. Sensitivity analyses will be conducted by examining outcomes under two alternative missing data management approaches, full information maximum likelihood (FIML) and multiple imputation [118]. The point estimates and 95% confidence intervals (CIs) of all effect sizes, Cohen’s *d* for continuous outcomes [119], as well as odds ratios [ORs] and risk ratios [RRs] for binary outcomes [120], will also be computed consistently.

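### Random-forest imputation is chosen partly for its behaviour under MNAR, yet neither it nor either named sensitivity analysis tests a departure from MAR

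*Protocol article*

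**What the plan says.** All of this is in the protocol article. Under Data processing and missing data management, the primary handling is fixed: "Random forest imputation with the *missRanger* package [116] will be used instead of multiple imputation". Two reasons are given. The forest copes better with nonlinear relations and interactions, and it "generates improved performance even under missing not-at-random (MNAR) conditions". The second reason carries a citation. The robustness checks are then named: "Sensitivity analyses will be conducted by examining outcomes under two alternative missing data management approaches, full information maximum likelihood (FIML) and multiple imputation".

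Under Sample size and power, the expected loss is large: "Accounting for an estimated 50% attrition rate, our planned sample size was 1,200 (600 participants per group"). Under Protocol adherence and engagement strategies, people may leave without a reason and owe no further procedures, so their later outcomes may be unobserved.

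No analysis elsewhere in the article relaxes MAR. The CACE analysis concerns engagement. The logistic multilevel model is a model check for binary outcomes.

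**The concern.** MNAR means that people with missing scores differ from people with the same observed history whose scores were seen. A random forest, however flexible, learns only from the observed scores. FIML, and MI as described here, condition on the same observed data. None of the three has a parameter for how leavers differ from comparable stayers.

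The plan therefore names MNAR as a reason for its primary method and then lists checks that cannot examine it. If the three results agree, a reader who has seen the MNAR wording may take that as protection against informative dropout. If non-improvers leave one arm more selectively than the other, all three estimates on GAD-7 and PHQ-9 move the same way, and comparing them does not show it.

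The arms differ enough for this to be plausible, though not shown. Both receive 126 prompts and the same brief momentary ratings. Digital PAI adds weekly 30-minute lessons and exercises of 1 to 2 minutes at each prompt.

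**Working it through.** **Inputs from the article.** 600 per arm, 50% attrition, 5% significance level (two-sided assumed), lower expected effect d = 0.2. The article gives no figure for bias or error rate under informative dropout, so there is none to reproduce. The sample-size range is not used here.

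**Assumptions not in the article.** Three standardised visits with correlation ρ = 0.6 between any two; all 50% of the loss at the final visit; baseline-adjusted ANCOVA at that visit as a stand-in for the piecewise multilevel model; bagged trees without predictive mean matching as a stand-in for missRanger; MI with 20 imputations. The log-odds of dropout rise by g per SD of the unseen final score (higher is worse). g = 0.25 is an odds ratio of 1.28, and g = 0.5 is 1.65.

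**Step 1: simulation with a true effect of zero, 1,000 trials per row, 50% missing in each arm throughout.**

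| Mechanism | FIML rejects | MI rejects | Bias, FIML and MI (SD) |
|---|---|---|---|
| MCAR | 4.8% | 4.2% | 0.00 |
| MAR, dropout on mid-treatment score, PAI only | 4.1% | 3.9% | 0.00 |
| Same MNAR in both arms, OR 1.65 | 4.7% | 4.1% | 0.00 |
| MNAR in PAI only, OR 1.28 | 18.3% | 17.7% | −0.07 |
| MNAR in PAI only, OR 1.65 | 53.3% | 51.3% | −0.13 |

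With complete data the same test rejects in 4.2%.

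**Step 2: closed-form check of the FIML rows.**
- Residual variance of the final score given the two earlier ones: 1 − 2ρ²/(1 + ρ) = 1 − 0.72/1.6 = 0.55.
- First-order shift in the mean of observed PAI scores at given history: g × residual variance × proportion missing. For g = 0.25: 0.25 × 0.55 × 0.5 = 0.069. For g = 0.5: 0.5 × 0.55 × 0.5 = 0.138. The simulation gave 0.068 and 0.131.
- Weight of the mid-treatment score: ρ/(1 + ρ) = 0.375. Variance of the estimate: 0.55 × 2/300 + 0.375² × (1 − 0.36) × 2/600 = 0.00367 + 0.00030 = 0.00397, so SE = 0.063.
- Rejection at the simulated biases: 0.068/0.063 = 1.08, giving Φ(1.08 − 1.96) ≈ 19%; 0.131/0.063 = 2.08, giving Φ(2.08 − 1.96) ≈ 55%. Both agree with the simulation within its error.

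**Step 3: range over the assumed correlation, OR 1.65, same formulas.**

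| ρ | Residual variance | First-order bias (SD) | SE | Rejection |
|---|---|---|---|---|
| 0.4 | 0.77 | 0.19 | 0.073 | about 75% |
| 0.6 | 0.55 | 0.14 | 0.063 | about 59% |
| 0.8 | 0.29 | 0.07 | 0.047 | about 34% |

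The first-order formula runs slightly high (59% here against 53% simulated at ρ = 0.6). A more informative observed history shrinks the problem but does not remove it.

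**Step 4: what a shift analysis would show.** A just-significant effect is 1.96 × 0.063 = 0.123 SD. With half of the PAI arm imputed, worsening the imputed scores by δ moves the estimate by 0.5δ. The tipping point is 0.123/0.5 ≈ 0.25 SD. None of the three stated analyses yields this number.

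**The case against.** The strongest reply has four parts.

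**The wording is comparative.** A reader might infer that the plan claims to have solved MNAR. It does not: it says, with a citation, that the forest performs better than MI even then. The simulated biases fit that as far as bias goes: −0.11 SD for the forest against −0.13 for FIML and MI at an odds ratio of 1.65. So the sentence needs qualifying, not striking out.

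**The checks do not simply echo the primary result.** A reader might infer that all three analyses will agree on a false positive. At an odds ratio of 1.28 the forest rejected in 37.1% of trials and all three jointly, in the same direction, in 15.6%. At least one check therefore failed to confirm 1 − 15.6/37.1 ≈ 58% of the forest's false rejections. Nor may the forest's own rates be put down to MNAR: it already rejects in about 16% under MCAR, because a single fill treats imputed values as observed. That is a separate fault, and FIML and MI can reveal it.

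**The mechanism is selected.** The same MNAR process in both arms produced no bias under the null. Nothing in the article shows dropout that differs by arm, or its direction. Heavier loss of non-improvers from control would bias against Digital PAI instead. The article also plans more repeated measures than the three visits simulated, which makes MAR more credible. All of this stands and limits the size, as Step 3 shows.

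**Detail may sit elsewhere.** An unseen analysis plan could add an MNAR analysis, and MI can itself carry a shift. But the article sets out the MNAR rationale and the checks together. The point rests on that stated pairing, not on an absence.

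**Conclusion.** The point holds in this form: the stated checks cannot test the one missing-data risk that the plan itself names, and half the sample is expected to be lost. If outcome-dependent dropout differs between arms, the primary fill, FIML and MI are all biased in the same direction. Equal dropout percentages would give no warning, since they were equal in every row of Step 1.

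At ρ = 0.6 and odds ratios of 1.28 to 1.65 per SD in one arm only, the FIML and MI bias is about 0.07 to 0.13 SD. That is roughly a third to two thirds of the d = 0.2 at the lower end of the expected effects. Their false-positive rate is about 18% to 53%. These rates are conditional on assumed odds ratios, correlations and direction, and are not a forecast for this trial. That all three methods share the MAR assumption does not depend on those values. This is a worthwhile, cheap improvement; it does not show that the planned efficacy analysis will mislead.

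**What to change.** In Data processing and missing data management:

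1. Qualify the MNAR wording so that it cannot be read as saying MNAR is handled, and describe the random-forest fill, FIML and MI as MAR-based.
2. Add one pre-specified MNAR sensitivity analysis for GAD-7 and PHQ-9: delta-adjusted MI that shifts imputed scores separately by arm over a range stated in advance, reporting the tipping point. Control-based imputation is an optional addition.
3. State beforehand which shifts count as plausible, and claim robustness to MNAR only if the conclusion survives them.

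This reuses the MI already planned and needs no new data. Recruitment was still under way when the article was written, so it can be fixed before allocation is revealed. The cost is a little extra analysis, and the efficacy conclusion may have to be stated as conditional on MAR.

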#### Statistical approaches for primary and secondary outcomes

Prospective analyses of primary and secondary continuous outcomes, such as anxiety and depressive symptom severity (GAD-7 and PHQ-9), anhedonia (DARS), and PA (PANAS), will be analyzed using multilevel modeling (MLM) with restricted maximum likelihood estimation (REML). Piecewise MLM will be used to assess between-group differences in changes across unique timeframes (e.g., baseline to post-treatment vs. post-treatment to 3-month follow-up), enabling the estimation of distinct linear slopes before and after critical time points to model nuanced changes in clinical outcomes over time. The MLM models will consist of fixed effects of group (Digital PAI vs. Self-Monitoring Placebo) and two-way group-by-time interaction to account for within-person associations. We will use the *nlme* package [121] for all analyses, assuming random intercepts and slopes for all models. Level 1 will model within-person changes over time, and Level 2 will capture between-person factors. All outcomes will be modeled across recurring time points (baseline, mid-treatment [Week 3], post-treatment [Week 6], as well as 3-month, 6-month, and 12-month follow-ups), aligned with this RCT’s assessment schedule. Covariates will include demographic variables (e.g., age, sex), baseline symptom severity, and device wear time, where relevant, for variables that significantly differed between groups at baseline. Between- and within-group effect sizes will be computed for all outcomes of interest [119, 122]. For binary clinical outcomes, such as depression remission indexed by PHQ-9 ≤ 4, generalized estimating equations (GEE) will be utilized to estimate between-group efficacy across all time points and follow-ups, accounting for repeated assessments with an exchangeable working correlation structure [123, 124]. Standard MLM with a logistic linking function will also be conducted as a sensitivity analysis for binary outcomes [125].

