### Study aims and hypotheses

Given the theories and logic outlined, this RCT implements a two-arm RCT that aims to evaluate the efficacy of a low-intensity, guidance-on-demand, 6-week Digital PAI vs. a Self-Monitoring Placebo control for adults with mild-to-moderate anxiety or depression. This Digital PAI was adapted from the 15-week face-to-face PAT [44], as detailed in the Method. It aims to equip individuals with diverse evidence-based ER skills that may enhance positive mood states and reduce anhedonia, including goal setting, gratitude, personal strengths, positive reappraisal, savoring, and exercises linked to reward sensitivity.

This RCT is unique in several ways. First, it examines how the Digital PAI might improve sleep outcomes. This inquiry is essential, given the high rates of sleep disturbances in anxiety and depressive disorders [45, 46]. Moreover, deficits in PA and reward sensitivity in anxiety and depression have been intimately linked to sleep disturbances [47, 48], which the Digital PAI may remedy. Second, the 12-month time horizon is relatively uncommon in DMHI trials [24], which facilitates the evaluation of long-term promises and pitfalls. Third, evaluating the efficacy of the Digital PAI in Singapore may advance implementation science across various cultures, thereby maximizing impact and scalability.

Our a priori hypotheses were twofold. First, we predicted that the Digital PAI would yield significantly greater improvements in anxiety and depression outcomes than the Self-Monitoring Placebo. Clinical outcomes were defined in binary terms, including remission indexed by Generalized Anxiety Disorder-7 (GAD-7) [49] and Patient Health Questionnaire (PHQ-9) [50] scores ≤ 4 as well as clinically significant improvement [51]. Clinical outcomes were also operationalized dimensionally, as scores from baseline to 6-week, 3-month, 6-month, and 12-month follow-ups. Second, we hypothesized that the Digital PAI would generate significantly more improvements in various secondary outcomes indexed dimensionally: anhedonia, attentional control, ER, generalized anxiety disorder (GAD) severity, negative affect (NA), panic disorder symptoms, perceived stress, PA, positive valence systems, self-compassion, sleep quality, and thinking errors.

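### The listed fixed effects omit time, and the within-segment slope comparison cannot by itself show distal efficacy on GAD-7 and PHQ-9; no contrast from baseline to follow-up is named

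*Protocol article*

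**What the plan says.** The model for the continuous outcomes is in the protocol article under *Statistical approaches for primary and secondary outcomes*.

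- Fixed effects: "The MLM models will consist of fixed effects of group (Digital PAI vs. Self-Monitoring Placebo) and two-way group-by-time interaction".
- Purpose: "Piecewise MLM will be used to assess between-group differences in changes across unique timeframes". The segments are given as an example: "baseline to post-treatment vs. post-treatment to 3-month follow-up". The stated gain is "enabling the estimation of distinct linear slopes before and after critical time points".
- Random effects: "assuming random intercepts and slopes for all models".

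*Sample size and power* says that the simulation "simulated a multilevel model with time and group as fixed effects".

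*Study aims and hypotheses* puts the dimensional form of the first hypothesis, greater improvement under Digital PAI, in terms of "scores from baseline to 6-week, 3-month, 6-month, and 12-month follow-ups".

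The *Discussion* credits the piecewise model with keeping proximal and distal outcomes apart. Between-group effect sizes are promised for every outcome, but no time point or contrast is given for the continuous ones. Binary outcomes get GEE estimates at all visits.

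**The concern.** There are two separate matters.

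First, the list of fixed effects has no time term, and it differs from the list in the power section. Neither list is the usual time, group and group-by-time model. What the listed model estimates then depends on how group is coded, which the article does not say. Shared improvement is plausible in this trial: entry requires raised GAD-7 and PHQ-9 scores, and Table 1 takes the pre-treatment values of both at screening, so regression to the mean is expected in both arms. A model that cannot represent a shared trend may attribute it to the intervention.

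Second, the comparison described for the period after treatment is a difference in slopes within that period. The hypothesis is about the difference in change since baseline. These are different quantities, and they diverge in the case the trial hopes to see, a benefit that lasts. Long-term benefit is a main aim, so the quantity that answers it should be named.

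**Working it through.** **Inputs from the article.** Six visits (baseline, Weeks 3 and 6, Months 3, 6 and 12); 600 per arm planned; 50% attrition; effect sizes d = 0.2 to 0.5; 5% significance level. 1,200 × 0.5 / 2 = 300 per arm after attrition.

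**Assumptions, not in the article.** Two-sided test; one knot at Week 6; baseline SD 1 (intercept variance 0.5, residual variance 0.5); random-slope variance 0 or 0.15 per segment; follow-up months counted from baseline or from Week 6; complete data on 300 or 600 per arm; variance components held at these values. Ranges below run over these choices.

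**Step 1. The plan's own figure.** Closed form, per arm: n = 2(1.960 + 0.878)² / d².
- d = 0.2: 403 per arm, 806 in total, 806 / 0.5 = 1,612, close to the stated upper figure of 1,600.
- d = 0.5: 65 per arm, 130 in total, 260 after attrition, against a stated 300.

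The article used simulation and gives no variance components, so the gap at the lower end is not part of this point. The figures also do not show which contrast was powered.

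**Step 2. The time term.** Let D = 1 for Digital PAI, p1 run from 0 to 1 over baseline to Week 6, and p2 from 0 to 1 over Week 6 to Month 12. The full model is

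E[Y] = β0 + β1·p1 + β2·p2 + γ0·D + γ1·D·p1 + γ2·D·p2.

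*Numeric 0/1 code, no time term.* β1 = β2 = 0, so the control line is flat and γ1 becomes the Digital PAI arm's own slope. With no treatment effect and both arms improving by 0.5 SD, γ1 is −0.50 instead of 0. Its standard error at 300 per arm is 0.050 to 0.056, so z is at least 0.5 / 0.056 = 8.9 in size and rejection is about 100%. With a shared change of only 0.1 SD, z is 0.1 / 0.056 = 1.8 to 0.1 / 0.050 = 2.0, and rejection is about 0.43 to 0.52.

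*Factor code in R.* With a single time variable, group plus group-by-time expands to an intercept, a group indicator and one slope per arm. That design has rank 4, as does the full model; the numeric version has rank 3. The fit is correct. Each printed slope coefficient tests one arm against zero, and the arm difference has to be requested.

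**Step 3. The distal contrast.** Take the full model with time included. Let Δ6 and Δ12 be the between-group differences in change from baseline at Week 6 and Month 12 (negative favours Digital PAI). Then γ1 = Δ6, γ2 = Δ12 − Δ6, and γ1 + γ2 = Δ12.

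| Truth | γ1 | γ2 | γ1 + γ2 |
|---|---|---|---|
| No benefit | 0 | 0 | 0 |
| 0.2 SD, fully maintained | −0.20 | 0 | −0.20 |
| 0.2 SD, half lost by Month 12 | −0.20 | +0.10 | −0.10 |
| 0.2 SD, fully lost by Month 12 | −0.20 | +0.20 | 0 |

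On γ2 the first two rows are identical. In the third row γ2 favours control although Digital PAI is still ahead.

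Rejection rates when 0.2 SD is fully maintained:

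| Contrast | 300 per arm | 600 per arm |
|---|---|---|
| γ1 (baseline to Week 6) | 0.72 to 0.81 | 0.95 to 0.98 |
| γ2 (later slope difference) | 0.05 | 0.05 |
| γ1 + γ2 (baseline to Month 12) | 0.64 to 0.79 | 0.91 to 0.97 |

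For example, with slope variance 0.15, months counted from baseline and 300 per arm, the standard error of the sum is 0.086; 0.20 / 0.086 = 2.33, and Φ(2.33 − 1.96) = 0.64. If the benefit is fully lost, γ2 is rejected 0.69 to 0.77 of the time at 300 per arm, in the direction of control.

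**The case against.** The strongest reply on the time term is that it was dropped in condensing. The surrounding sentences speak of distinct slopes, random slopes and within-person change over time, and the power section names time. A flat control arm would contradict all of these. The work is to be done in R, where a factor code is natural and the fit would be right. This largely stands: the omission is probably wording, and false rejection arises only under numeric coding. The mismatch between the two stated lists remains.

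On the segments, the reply is that they are introduced as an example, that nothing makes the later slope difference the sole or deciding test, and that such a contrast is a proper measure of maintenance or relapse, which the article also wants to study. The difference from baseline to Month 12 is a linear combination from the same model. All of this is fair, and a 5% rejection rate for a true zero is correct behaviour for that contrast. But the within-segment comparison is the only between-group comparison described for continuous change, and the *Discussion* links it to distal outcomes. The promised effect sizes name no contrast, and the GEE analysis covers binary outcomes only.

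A full analysis plan that is not shown may state the formula. The point concerns what the article does state: two lists that differ, and a comparison that does not match its hypothesis.

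**Conclusion.** The point holds as a correction to the stated model and contrasts. The listed fixed effects omit time and do not match the power section. The later slope difference cannot by itself show distal efficacy on continuous GAD-7 and PHQ-9, because it is zero when a benefit is fully maintained and favours control when it partly fades. That result is algebra and needs no assumption about variances. The power ranges do rest on the assumed variance components, visit timing and complete data.

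A reader might go further, and the documents do not support it:
- *That the plan does not test its hypotheses.* The first segment tests the Week 6 part once time is included, GEE tests the binary form at all visits, and the planned model can yield the cumulative contrast.
- *That false rejection is certain.* It requires numeric coding, and its size depends on the shared change.
- *That a lasting benefit will be reported as no distal efficacy.* No such decision rule is stated.
- *That the power simulation had no interaction.* A one-clause summary does not show this; it only fails to say which contrast was powered.

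**What to change.** 1. State the fixed effects as time (each piece, or visit as a category), group, and group-by-time.
2. Define the efficacy test for GAD-7 and PHQ-9 as the model-implied between-group difference in change from baseline at Week 6, Month 3, Month 6 and Month 12. In the piecewise model this is the sum of the group-by-time pieces up to that visit.
3. Report the post-treatment slope difference only as maintenance or loss of gain.
4. Describe the power simulation on the same model and contrast.

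The cost is a few sentences and the contrast code. No new data or change to trial conduct is needed. The article reports that data collection is ongoing and that the analyst stays blinded until it ends, so the change can be made before any comparison by arm is seen.

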## Method

### Study design

Details about this trial are captured in the SPIRIT (Standard Protocol Items: Recommendations for Interventional Trials) checklist [54, 55] in Appendix A of the online supplemental materials (OSM) and Fig. 1. This study is a two-arm, parallel-group RCT that aims to test the efficacy of Digital PAI relative to a Self-Monitoring Placebo control in adults with mild-to-moderately severe anxiety or depression. After providing informed consent and completing the Qualtrics-administered baseline self-report battery, participants will be randomized in a 1:1 ratio (*n* = 600 per condition) using a computer-generated random number sequence embedded in the Qualtrics platform. In other words, participants are randomized into the Digital PAI or Self-Monitoring Placebo control group at the end of the baseline assessment using the built-in randomizer function in Qualtrics. The sequence is stratified by race and sex to ensure balanced allocation across key demographic strata. Immediately after completing the baseline assessment, Qualtrics automatically assigns participants to either the 6-week, low-intensity, guidance-on-demand Digital PAI or the 6-week Self-Monitoring Placebo, both of which are accessed via the mEMA Ilumivu software. The allocation sequence is concealed from the lead principal investigator (PI) and study analyst via automated assignment coding; both remain blinded to treatment group assignments until after data collection is complete.

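### The primary model leaves the baseline group difference free and adjusts for baseline severity only when it differs significantly between arms, by a covariate that cannot change the group-by-time estimate

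*Protocol article*

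**What the plan says.** Three statements in the protocol article, under Statistical approaches for primary and secondary outcomes, fix the model for GAD-7, PHQ-9 and the other repeated continuous outcomes.

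- Baseline is an outcome row: "All outcomes will be modeled across recurring time points (baseline, mid-treatment [Week 3], post-treatment [Week 6], as well as 3-month, 6-month, and 12-month follow-ups".
- The fixed effects are "fixed effects of group (Digital PAI vs. Self-Monitoring Placebo) and two-way group-by-time interaction to account for within-person associations". The group main effect lets the two arms have different baseline means.
- On adjustment: "Covariates will include demographic variables (e.g., age, sex), baseline symptom severity, and device wear time, where relevant". The sentence then limits covariates to variables with a significant baseline difference between arms. On the natural reading, that condition governs baseline severity too.

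The same section specifies random intercepts and slopes and a piecewise time trend. The section on missing data imputes by random forest before the main analysis, so the analysed data set is balanced. Under Sample size and power, the protocol plans 1,200 participants with 50% attrition and expects effects from d = 0.2 to d = 0.5. It gives no variance components and no correlation between baseline and follow-up.

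**The concern.** Baseline adjustment in a randomised trial should remove the part of the treatment estimate that comes from chance imbalance in the starting score, and should gain precision. As described here it does neither.

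If the arms differ significantly on baseline GAD-7, the GAD-7 score enters as a covariate in a model where it is already the first outcome value. A quantity that is constant within a person cannot alter a contrast of within-person change, so the adjustment is inert exactly where it is invoked. If the arms do not differ significantly, nothing is adjusted.

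There is a second, separate matter. With the baseline group difference left free, the group-by-time contrast is a difference in change from baseline, whether or not the covariate enters. That is unbiased under randomisation, but it uses the baseline score less efficiently than the same data allow. Both primary outcomes are affected.

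**Working it through.** **The plan's own figure.** Inputs from Sample size and power: 5% level (two-sided assumed), 81% power, d from 0.2 to 0.5, 50% attrition. Per arm, n = 2[(1.960 + 0.878)/d]².

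- d = 0.2: 403 per arm, 806 in total; 806/(1 − 0.5) = 1,612, close to the stated upper end of 1,600.
- d = 0.5: 65 per arm, 130 in total; 130/(1 − 0.5) = 260, against the stated lower end of 300.

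This simple formula reproduces only the upper end. The stated range comes from a simulation whose inputs are not given, so the protocol's figures cannot supply r. After 50% attrition, 600 completers remain, 300 per arm.

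**Does the covariate act?** With two time points, write person i's outcomes as y_i0 and y_i1, and let a main-effect covariate x_i add βx_i to both. In y_i1 − y_i0 the term cancels, so the group-by-time estimate is the same with or without it. Simulated complete data with mixed models agreed: −0.2132 without the baseline covariate and −0.2132 with it. On data with unimputed dropout, the estimates shifted slightly, by up to about 0.02.

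The effect on the standard error depends on the random effects:

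- random intercept only: 0.0718 without and 0.0718 with;
- random intercept and slope: 0.0737 without and 0.0830 with;
- in a separate six-visit simulation at r = 0.5: essentially unchanged with one random slope, but 0.0759 to 0.0877 with two piecewise random slopes.

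**What imbalance is left in?** With equal SDs, a difference in change carries an expected error of −(1 − r) times the baseline imbalance. The smallest significant imbalance is 1.96 × √(2/n) SD.

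- 600 per arm (all randomised; the baseline battery precedes randomisation): 0.113 SD. For r from 0.4 to 0.7 the error is 0.6 × 0.113 = 0.068 down to 0.3 × 0.113 = 0.034 SD.
- 300 per arm (completers only): 0.160 SD, with error 0.096 down to 0.048 SD.

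The main-effect covariate leaves these errors as they are. The trigger fires in about 5% of trials per measure, or 1 − 0.95² = 9.75% for at least one of GAD-7 and PHQ-9 if independent.

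**Precision forgone.** In units of the outcome SD, the change score has SD √(2(1 − r)) and the baseline-adjusted outcome has SD √(1 − r²). Power = Φ(d/(SD × √(2/n)) − 1.960). At r = 0.5 with n = 300 and d = 0.2, √(2/300) = 0.0816:

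- change: SD 1.000, 0.2/0.0816 = 2.449, power 68.8%;
- adjusted: SD 0.866, 0.2/(0.866 × 0.0816) = 2.828, power 80.7%.

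| r (assumed) | Change, 300 per arm | Adjusted, 300 per arm | Gap (points) | Gap, 600 per arm |
|---|---|---|---|---|
| 0.3 | 54.4% | 72.8% | 18.4 | 11.9 |
| 0.4 | 60.9% | 76.2% | 15.3 | 8.0 |
| 0.5 | 68.8% | 80.7% | 12.0 | 4.6 |
| 0.6 | 78.2% | 86.5% | 8.3 | 1.9 |
| 0.7 | 88.5% | 92.9% | 4.4 | 0.4 |
| 0.8 | 97.2% | 98.3% | 1.1 | 0.0 |

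The table is for d = 0.2. At d = 0.3 with 300 per arm, the gap is 6.1, 3.2 and 1.2 points at r = 0.4, 0.5 and 0.6. At d = 0.5 it is nil for r from 0.4 up.

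A piecewise generalised least squares calculation at d = 0.2 with 300 per arm compared a free with a common baseline mean. Gaps on three visits were 17.3, 13.1 and 8.9 points at r = 0.4, 0.5 and 0.6; on all six visits they were 17.4, 12.1 and 7.1.

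**The case against.** The strongest reply is that a longitudinal model with baseline as an outcome and a free group effect is a standard, valid analysis: under randomisation it is unbiased. In simulation without the covariate, its model standard error matched the empirical one (0.0759 for both at r = 0.5). Not choosing the most efficient estimator is not an error. That stands, and the point is therefore an improvement in precision and in protection against chance imbalance, not a claim of invalid inference.

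It can also be said that the protocol does not state that baseline severity means the outcome's own score, nor whether it would interact with time. That stands in part. For an anhedonia model, GAD-7 or PHQ-9 severity is a different variable. For the two primary outcomes, however, the outcome's own baseline score is the obvious reading.

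Two stronger readings are tempting and are not supported:

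- A reader who stops at the list of covariates might infer that baseline always sits on both sides of the model. The rest of the sentence makes this conditional on a significant difference.
- A reader might infer that the double use itself costs 8 to 16 points of power. Gaps of that size come from comparing a free with a common baseline mean, neither with the covariate. Dropping the covariate alone recovers none of that gap. Nor is a general loss from a wider standard error established, since any inflation depends on the random-effects form, which the protocol gives only in outline.

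**Conclusion.** The concern holds in two limited parts.

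First, the baseline adjustment is badly fixed. It hangs on a significance test, and when triggered for the outcome's own score as a main effect it leaves the group-by-time estimate unchanged on balanced data. Including baseline severity in every case would not repair this while baseline remains an outcome row with a free group effect.

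Second, the free baseline group effect gives up precision whether or not the covariate enters. At d = 0.2 with 300 completers per arm, the two-time-point loss runs from about 15 points at r = 0.4 to about 1 at r = 0.8. It is smaller with more completers or a larger effect, and a multi-visit model can give somewhat larger gaps, depending on the assumed covariance.

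These sizes rest on assumed correlations, a two-sided test and equal SDs at baseline and follow-up. If SDs differ, the variance saved by adjustment is (s0 − r·s1)², where s0 and s1 are the baseline and follow-up SDs. Because eligibility restricts baseline scores to fixed ranges, s0 may be below s1, which would change the gap. The direction does not reverse.

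**What to change.** Use baseline once, and drop the significance trigger for it. Either form works:

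- **(a)** Keep baseline as an outcome row, remove the group main effect so that both arms share one baseline mean (time terms plus group-by-time terms), and leave the outcome's own baseline score out of the covariates.
- **(b)** Model Week 3 to Month 12 only, and always include the outcome's own baseline score and its interaction with time, whatever imbalance is observed.

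Apply the same form to GAD-7, PHQ-9 and the repeated continuous secondary outcomes. Quote any expected power gain as a range under a stated correlation.

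The cost is a sentence of analysis wording and a changed model formula. It needs no new data or participants and relies only on randomisation. The coefficient then describes the effect at an equal baseline and not a raw difference in change, which the report should say. The protocol describes recruitment as ongoing, so the change can be made and dated before unblinding.
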